## Abstract

**Introduction:**

Idiopathic non-obstructive azoospermia (NOA) is a severe form of male infertility with limited non-surgical treatment options. Microdissection testicular sperm extraction (micro-TESE) remains the standard approach for sperm retrieval, yet success rates vary substantially, and many patients undergo surgery without successful sperm recovery. Hormonal optimization using human chorionic gonadotropin (hCG) with or without follicle-stimulating hormone (FSH) has been proposed to improve spermatogenesis in hypogonadal men, but evidence from randomized controlled trials is lacking. This multicenter trial evaluates whether gonadotropin-based hormonal optimization improves sperm availability for intracytoplasmic sperm injection (ICSI) compared with standard-of-care (SOC) management in men with idiopathic NOA and biochemical hypogonadism.

**Methods and analysis:**

This multicenter, randomized, controlled, parallel-group superiority trial will allocate participants 1:1 to hormonal therapy or SOC. Eligible participants are men with idiopathic NOA, total testosterone <350 ng/dL on two fasting morning tests, and FSH ≥7.6 IU/L, consistent with APHRODITE Groups 3–4. Key exclusion criteria include cryptorchidism, prior chemotherapy or radiotherapy, defined genetic NOA (e.g., AZFa/complete AZFb deletions), prior micro-TESE, recent hormonal therapy use, uncontrolled endocrine disease, severe liver disease, polycythemia, active malignancy, inability to comply with the study procedures, and clinically significant varicocele. Participants assigned to the intervention arm will receive gonadotropin-based hormonal optimization using hCG and recombinant FSH, with hormonal monitoring and hCG dose titration throughout treatment. The control arm will receive standard management without hormonal therapy. The primary endpoint is a composite treatment-policy outcome defined as sperm availability suitable for ICSI at any time from randomization through Week 16, either through ejaculated sperm or through micro-TESE. Secondary outcomes include micro-TESE sperm retrieval success rate, need for surgery, embryologic outcomes, reproductive outcomes, and treatment safety. The study is designed as a pragmatic comparative effectiveness trial that intends to evaluate whether biologically informed hormonal optimization improves clinically meaningful sperm availability under routine clinical practice conditions.

**Ethics and Dissemination:**

The study was approved by Institution Ethics Committee (IIVF-UA00l 00).

**Clinical Trial Registration:**

(https://clinicaltrials.gov/study/NCT07540611), identifier NCT07540611.

## Introduction

Non-obstructive azoospermia (NOA) represents the most severe form of male infertility and affects approximately 10%–15% of infertile men (1). In men with idiopathic NOA, impaired intratesticular testosterone production and elevated follicle-stimulating hormone (FSH) levels often reflect underlying Sertoli cell dysfunction and reduced spermatogenic capacity (2). Currently, microdissection testicular sperm extraction (micro-TESE) remains the preferred method of sperm retrieval in these patients, offering the highest likelihood of obtaining sperm for intracytoplasmic sperm injection (ICSI). However, sperm retrieval success rates remain highly variable, generally ranging from 40% to 60%, and many men undergo invasive surgery without successful sperm recovery (3, 4).

Despite extensive investigation, reliable preoperative predictors of sperm retrieval remain inconsistent across studies and populations. Several clinical, hormonal, and molecular biomarkers have been explored, including FSH, inhibin B, anti-Müllerian hormone, and testicular histopathology, but no single marker has demonstrated sufficient predictive accuracy for routine clinical use. Representative studies evaluating biomarkers and predictors of sperm retrieval success in idiopathic NOA are summarized in Table 1.

**Table 1 T1:** Clinical studies involving predictors/biomarkers for sperm retrieval in idiopathic NOA and related micro-TESE outcomes.

Year	Reference	N	Population	Sample type	BM(s)	Threshold (cutoff)	Sens	Spec
2023	Deng et al. (14)	168	Idiopathic NOA undergoing micro-TESE	Serum	INHB; AMH; INHB/AMH	INHB 21.51 pg/mL; INHB/AMH 3.19	86.3% (INHB/AMH)	53.8% (INHB/AMH)
2021	Zarezadeh et al.(17)	—	NOA (predictors review)	Serum/seminal (review)	FSH, LH, TT, INHB, AMH, E2, PRL, leptin (various)	Heterogeneous; no unified cutoffs	—	—
2021	Majzoub et al. (with S.C. Esteves) (16)	297	NOA; staged Testicular Sperm Aspiration (TESA) → micro-TESE	Clinical/serum	Multivariable model (age, testis size, FSH, etc.)	Model-based (no single threshold)	NR	NR
2021	Shiraishi et al. (18)	76	NOA vs. OA; subset on anastrozole	Testicular fluid/serum/tissue	Intratesticular T and E2, aromatase expression	No diagnostic cutoff; mechanistic	—	—
2023	Shi et al. (15)	114	Idiopathic NOA, micro-TESE	Testicular tissue	circ_MGLL (circRNA) + clinical nomogram	Nomogram (probability-based)	-	-
2021	Achermann et al. (Review) (1)	4,895 (across 116 studies)	NOA; micro-TESE effectiveness and complications	—	—	SRR ∼46.6% overall; naïve ∼46.8%	—	—
2024	Mahdy et al. (2)	172	NOA, micro-TESE	Clinical/serum/histology	Histology; clinical factors	NR	—	—

BM, biomarker; INHB, inhibin B; AMH, anti-Müllerian hormone; TT, total testosterone; Spec, specificity; Sens, sensitivity; NPV, negative predictive value; NR, not reported.

Emerging evidence suggests that optimization of the hypothalamic–pituitary–gonadal axis, particularly correction of hypogonadism prior to surgical sperm retrieval, may enhance spermatogenic output and potentially improve the likelihood of extracting sperm at surgery (3). However, robust randomized controlled data assessing the efficacy of gonadotropin therapy in idiopathic NOA are lacking.

To improve phenotypic stratification and guide therapeutic decision-making, Esteves et al. proposed the APHRODITE criteria, a clinically oriented classification system based on patient characteristics, semen profile, and readily available hormonal parameters, particularly FSH and total testosterone (TT) levels (5).

The APHRODITE criteria were specifically developed to identify subgroups of men with idiopathic infertility and/or hypogonadism in whom endocrine modulation may be endocrinologically and clinically relevant (5).

Within this scheme, men classified as APHRODITE Groups 3 and 4 exhibit biochemical hypogonadism associated with within normal ranges or elevated FSH levels, suggesting partial but potentially recoverable testicular dysfunction. In these individuals, physiologic restoration of the hypothalamic–pituitary–gonadal axis using human chorionic gonadotropin (hCG), with or without adjunctive recombinant FSH, has been proposed as a strategy to improve intratesticular hormonal support, enhance Sertoli cell function, and potentially stimulate residual spermatogenesis (6). Observational studies and systematic reviews have suggested a possible association between hormonal optimization and improved sperm retrieval outcomes in selected NOA populations (1, 6, 7), although high-quality randomized evidence remains lacking.

To address this critical evidence gap, we designed a multicenter, randomized, controlled superiority trial comparing a structured gonadotropin-based hormonal optimization strategy versus standard-of-care (SOC) management in hypogonadal men with idiopathic NOA classified within APHRODITE Groups 3 and 4. The trial evaluates whether hormonal therapy improves sperm availability for ICSI within a 16-week treatment window, either through ejaculated sperm or micro-TESE. Importantly, the study was designed as a pragmatic comparative effectiveness trial rather than a placebo-controlled efficacy study, aiming to determine whether a biologically informed hormonal optimization strategy improves clinically meaningful sperm availability for ICSI under routine clinical practice conditions.

## Method and analysis

### Study objective

The primary objective of this multicenter randomized controlled trial is to determine whether physiologic gonadotropin-based hormonal optimization (hCG with FSH) increases the likelihood of obtaining sperm suitable for ICSI—either through ejaculated sperm or through micro-TESE—within 16 weeks in hypogonadal men with idiopathic NOA, compared with SOC management without hormonal therapy.

The secondary objective is to evaluate the impact of hormonal therapy on surgical sperm retrieval rates, need for surgery, embryologic outcomes (fertilization, blastulation, blastocyst quality), and reproductive outcomes including clinical pregnancy, miscarriage, and live birth, as well as to assess treatment safety.

We primarily hypothesize that gonadotropin-based hormonal optimization (hCG + FSH) will increase the proportion of men with idiopathic NOA who achieve sperm availability for ICSI—either through ejaculated sperm or through micro-TESE—by Week 16, compared with standard-of-care management.

Our secondary hypothesis is that hormonal therapy will reduce the need for micro-TESE compared with standard-of-care and improve surgical sperm retrieval rates among men undergoing micro-TESE.

### Population

The inclusion criteria are as follows: idiopathic NOA; hypogonadal (TT <350 ng/dL on two fasting morning tests); and FSH ≥7.6 IU/L (APHRODITE Group 3: 7.6–12.0 IU/L; Group 4: >12.0 IU/L). The exclusion criteria are as follows: cryptorchidism, chemo/radiation, genetic NOA (e.g., AZFa/complete AZFb), testicular trauma/torsion, postorchitis; prior micro-TESE within 12 months; recent gonadotropin therapy (<6 months); uncontrolled endocrine disease; active malignancy; severe liver disease; polycythemia (Hct > 50%); inability to comply; and varicocele ≥Grade 3.

### Study design and methods

This multicenter, randomized, controlled, parallel-group superiority trial assigned men 1:1 to hormonal therapy or SOC. Eligible participants had idiopathic NOA, total testosterone <350 ng/dL on two fasting morning tests, and FSH ≥7.6 IU/L (APHRODITE Groups 3–4). Key exclusions included cryptorchidism, prior chemotherapy/radiation, genetic NOA (AZFa/complete AZFb deletions), prior micro-TESE within 12 months, recent gonadotropin use, uncontrolled endocrine disease, severe liver disease, polycythemia, active malignancy, inability to comply, and presence of untreated clinical varicocele requiring correction. Table 2 illustrates the summary of the study design.

**Table 2 T2:** Summary of study design.

Design	Multicenter, randomized, controlled, parallel-group superiority trial (1:1)
Population	Idiopathic NOA; hypogonadal (TT <350 ng/dL on two fasting morning tests); FSH ≥7.6 IU/L (APHRODITE Group 3: 7.6–12.0 IU/L; Group 4: >12.0 IU/L). Exclusions: cryptorchidism, chemo/radiation, genetic NOA (e.g., AZFa/complete AZFb), testicular trauma/torsion, postorchitis. prior micro-TESE within 12 months; recent gonadotropin therapy (<6 months); uncontrolled endocrine disease; active malignancy; severe liver disease; polycythemia (Hct > 50%); inability to comply. Varicocele ≥ Grade 3
Interventions	Arm A: hCG + FSH therapy with monthly hormone-driven titration (hCG initial ∼83 µg SC twice weekly; no preset min/max; target TT >350–900 ng/dL) + FSH 150 IU SC twice weekly (increase to 150 IU SC three times weekly if ‘FSH reset’ < 1.5 IU/L); allow anastrozole 1 mg PO daily/letrozole 2.5 mg half-tablet alternate day if T/E < 10. Arm B: Standard-of-care (SOC) no gonadotropins
Follow-up	Participants in both arms will be followed up from randomization through Week 16 for ascertaining the primary composite endpoint. The SOC arm may undergo micro-TESE at any time within this window per standard scheduling; a semen analysis will be performed on the day of surgery to capture rare ejaculated sperm. The hormonal arm will undergo semen analyses at Weeks 12 and 16, with micro-TESE at Week 16 if ejaculated sperm is absent. No artificial delay is imposed on the SOC arm
Primary outcome	Success is defined as sperm available for ICSI at any time from randomization through Week 16 via ejaculation or micro-TESE, centrally adjudicated, and blinded to allocation
Secondary outcomes	Micro-TESE SSR; need for surgery; safety/harms; ICSI fertilization; blastulation rate; blastocyst quality; top-1quality blastocyst rate; clinical pregnancy rate; miscarriage rate; live birth (exploratory)
Randomization/concealment	Central web-based randomization; permuted variable blocks; stratified by site and APHRODITE group; allocation concealed
Masking	Blinded lab personnel/embryologists and central adjudicators; surgeons/participants unblinded
Estimand	Treatment-policy estimand per ICH E9(R1) for composite outcome up to Week 16. To address potential bias from differential procedure timing, the primary analysis uses a fixed landmark at Week 16 (treatment policy). A time-to-event secondary analysis (time to first sperm availability) will be performed to assess consistency
Semen test on surgery day	Control arm performs a semen analysis on the day of micro-TESE to capture rare ejaculation successes
Interim	Safety-only interim at approximately 50% randomized (≥12-week follow-up); no efficacy/futility testing
BSSR	Blinded sample size re-estimation when ≥30% have completed Week-16 outcomes; adjust total N for nuisance event rate (cap +20%)

The trial flowchart is provided in Figure 1.

**Figure 1 F1:**
[figure not shown]
Flowchart for NOA Protocol; FSH, follicle-stimulating hormone; HCG- SOC, standard of care, HCG, human chorionic gonadotropin; SSR, surgical sperm retrieval, HPE, histopathological examination.

### Interventions

**Arm A (Hormonal therapy):**
hCG initial dose: ∼83 µg SC twice weekly; monthly titration guided by hormone levels with no preset min/max to maintain TT >350–900 ng/dL.Monthly endocrine panel: TT, E2, LH, and FSH (plus CBC/Hct, LFTs, lipids) for titration and safety.FSH: 150 IU SC twice weekly (fixed); escalation to 150 IU SC three times weekly if “FSH reset” was observed (FSH <1.5 IU/L). The threshold of FSH <1.5 IU/L was selected to identify excessive suppression of endogenous pituitary FSH secretion during hCG therapy. This threshold was physiologically derived from evidence demonstrating that profound FSH deficiency adversely affects Sertoli cell function and spermatogenesis, particularly in hypogonadotropic states (8–10). In addition, observational data from hypogonadal NOA men receiving hCG-based hormonal therapy demonstrated that approximately 20% of patients developed profound endogenous FSH suppression below this threshold during hCG stimulation, which normalized after escalation of exogenous recombinant FSH therapy (11–13).Aromatase inhibitor: anastrozole 1 mg PO daily/letrozole 2.5 mg half-tablet alternate day if T(ng/dL)/E(pg/mL) < 10; reassess monthly and taper if normalized.Week 12 semen analysis: if ejaculated sperm adequate for ICSI → success; cryopreserve; treatment may stop; otherwise, continue to Week 16.**Arm B (SOC):** No gonadotropin therapy; micro-TESE could occur anytime within 16 weeks.

### Follow-up

Hormonal therapy participants underwent semen analyses at Weeks 12 and 16, with micro-TESE at Week 16 if no ejaculated sperm were present. SOC participants underwent semen analysis on the day of micro-TESE to detect rare ejaculated sperm. All participants were followed up through Week 16.

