#### Statistical model and test of interaction

The analysis will be interaction-driven. Treatment effects within subgroups will be descriptive unless the treatment-by-subgroup interaction is statistically significant.

A generalized linear model (identity link, robust standard errors) shown in Equation 1 will be used:$$Y\_i\;=\beta_{0\;}+\beta_{1}\cdot \mathrm{Treatment}\_i+\beta_{2}\cdot \mathrm{Group}\;4\_i+\beta_{3}\cdot (\mathrm{Treatment}\_i\times \mathrm{Group}\;4\_i)+\gamma^{T}X\_i+u\_\mathrm{site}+\varepsilon \_i,$$(1)where Y_i represents the binary composite outcome (sperm available for ICSI by Week 16), Group 4_i is an indicator variable for APHRODITE Group 4, and X_i denotes prespecified covariates (female age, male age, center, baseline semen parameters, baseline TT/E2, baseline DNA Fragmentation Index (DFI), and number of Metaphase II (MII)). The interaction term *β*_3_ tests for a differential treatment effect between Groups 3 and 4. Random intercepts for site will account for clustering, and results will be presented as marginal risk differences.

The test for interaction will use a two-sided *α* = 0.05. Although prospectively specified and biologically motivated, subgroup analyses are considered supportive and hypothesis-generating unless sufficiently large interaction effects are observed. The trial is primarily powered for the overall treatment effect rather than formal interaction testing. The Table 3 illustrates SPIRIT schedule for enrollment, intervention, and assessments.

**Table 3 T3:** SPIRIT schedule of enrollment, interventions, and assessments.

Procedure/time point	Enrollment (≤28 days)	Baseline (W0)	W12	W16
Eligibility and consent	X			
Randomization		X		
hCG + FSH (Arm A)		X	X	X
Endocrine labs (TT, E2, LH, FSH; CBC/Hct, LFTs, lipids)		X	X	X
Semen analysis		X	X	X
Micro-TESE (if needed)				X
AE/SAE assessment		X	X	X

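### Safety assessment stops at Week 16, when Arm A has its scheduled micro-TESE, so the comparison of surgical harms after the day of surgery is tilted towards Arm A

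*Protocol article*

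**What the plan says.** The Study objective section includes safety among the secondary aims ("as well as to assess treatment safety"), and the Outcomes section and Table 2 list harms as a secondary outcome.

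The timing of surgery differs by arm:
- Arm A: Table 2 schedules surgery "with micro-TESE at Week 16 if ejaculated sperm is absent", and the Follow-up section agrees ("with micro-TESE at Week 16 if no ejaculated sperm were present"). The Sensitivity analyses and Estimands sections also foresee elective early surgery at 12 weeks.
- SOC: "The SOC arm may undergo micro-TESE at any time within this window per standard scheduling". Table 2 adds that this arm is not to be artificially delayed.

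Observation ends at one calendar point for everyone. Table 2 says "Participants in both arms will be followed up from randomization through Week 16 for ascertaining the primary composite endpoint". The Follow-up section is unqualified: "All participants were followed up through Week 16". In Table 3 the row "AE/SAE assessment" is marked at W0, W12 and W16, and there is no later column.

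Two further statements bear on the point. The interim review is described in Table 2 as "Safety-only interim at approximately 50% randomized (≥12-week follow-up". The section on interim analysis says that a missing AE or SAE counts as no event unless site monitoring or DSMB review shows otherwise.

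**The concern.** Time at risk after surgery is fixed by the schedule, and it is fixed differently in the two arms. An SOC man operated on early has later assessments at which a complication can be reported. An Arm A man operated on as scheduled has none after the day of surgery. Perfect adherence and complete data would not remove the difference.

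The trial could then report fewer surgical complications per operation in the hormonal arm when the true risk is equal. Reading unrecorded events as absent makes this worse, because a postoperative period that nobody observed may be tabulated as event-free. Events that were never collected cannot be recovered at analysis, so the matter has to be settled in the schedule.

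**Working it through.** The plan gives no figure for postoperative observation, so there is none to reproduce. The sample size is not involved.

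**Step 1: scheduled observation.** The last AE/SAE assessment is at Week 16, so postoperative observation = 16 − week of surgery.
- Arm A, scheduled surgery: 16 − 16 = 0 weeks.
- Arm A, elective surgery at Week 12: 16 − 12 = 4 weeks.
- SOC: between 16 − 16 = 0 and 16 − 0 = 16 weeks.

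The distribution of SOC surgery dates is not given. If uniform over Weeks 0–16, the SOC mean is 16 − 8 = 8 weeks; over Weeks 0–8 it is 12; over Weeks 8–16 it is 4; if all surgery is at Week 16 it is 0.

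**Step 2: size of the artefact.** These inputs are assumptions, not figures from the documents:
- true complication rate per operation r = 5%, equal in both arms;
- share q of complications on the day of surgery, recordable in both arms;
- the remainder have exponential onset with mean m = 1, 2 or 4 weeks;
- all Arm A surgery is at Week 16.

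Recorded rate in Arm A = r × q.
Recorded rate in SOC = r × [q + (1 − q) × s], where s is the share of later complications that begin by Week 16.
Spurious gap = r × (1 − q) × s.

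For SOC surgery uniform over the last L weeks before Week 16, s = 1 − (m/L)(1 − e^(−L/m)).
- L = 16: s = 0.938 (m = 1), 0.875 (m = 2), 0.755 (m = 4).
- L = 8: s = 0.875, 0.755, 0.568.
- All SOC surgery at Week 16: s = 0.

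| SOC surgery | q | Arm A recorded | SOC recorded | Gap (points) |
|---|---|---|---|---|
| Weeks 0–16 | 0 | 0% | 3.8%–4.7% | 3.8–4.7 |
| Weeks 0–16 | 0.5 | 2.5% | 4.4%–4.8% | 1.9–2.3 |
| Weeks 8–16 | 0 | 0% | 2.8%–4.4% | 2.8–4.4 |
| Weeks 8–16 | 0.5 | 2.5% | 3.9%–4.7% | 1.4–2.2 |
| All at Week 16 | 0.5 | 2.5% | 2.5% | 0 |

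The gap is proportional to r. Within these scenarios it is never negative, and it is zero only when all SOC surgery is also at Week 16. Elective Week 12 operations in Arm A would narrow it.

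**Step 3: effect of an equal window.** If every operation is followed for the same period, s is the same in both arms and the gap is 0. A 4-week window would capture 98%, 86% or 63% of later complications for m = 1, 2 or 4. The longer the onset, the less is captured, but equally in each arm.

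**The case against.** The strongest reply is that this is a condensed article. A full protocol may hold a postoperative visit, and Table 3 is plainly not exhaustive: it omits the monthly laboratory panel required under Interventions, marks micro-TESE only at W16 although SOC surgery may come earlier, and has no column for pregnancy or live birth. Table 2 also ties the Week 16 window to the primary endpoint, and the reproductive outcomes imply later contact. This lowers certainty about what sites will do in practice. It does not supply an AE assessment after Week 16. The article states a schedule and an end of follow-up, and both need correcting if another document differs.

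The Limitations section acknowledges the difference in surgical timing and points to sensitivity analyses and the treatment-policy estimand. It does not mention harms, and those analyses cannot restore events that were not collected.

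Three stronger readings are tempting, and the documents do not support them.
- *The whole safety comparison favours Arm A.* Harms of the hormonal regimen during treatment fall inside the assessed window. Arm A also has monthly safety laboratory tests with no stated SOC equivalent, which could raise its recorded events. The net direction for overall safety is not determined.
- *Arm A surgical harms cannot be seen at all.* Intraoperative and same-day events can be recorded at the Week 16 assessment, and elective Week 12 surgery leaves 4 weeks.
- *The interim review necessarily precedes all Arm A surgery.* Twelve weeks is a minimum, so with staggered entry some men may be past Week 16. For those men, however, no assessment after a Week 16 operation is scheduled either.

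**Conclusion.** The point holds for surgical harms arising after the day of surgery. As scheduled, they are largely unobserved in Arm A and observed for 0 to 16 weeks in SOC, so the comparison of surgical harms is biased in favour of Arm A unless all SOC surgery is at Week 16. The rule that a missing AE means no event adds to the bias.

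The direction follows from the stated schedule. The size does not, because the documents give neither a complication rate nor the spread of SOC surgery dates. At an assumed equal true rate of 5%, with SOC surgery uniform over Weeks 0 to 16, the artefact is about 2 points if half of complications are same-day and about 4 to 5 points if none are. It is smaller if SOC surgery comes late. The primary endpoint and its analysis are untouched, so this is a cheap improvement to a secondary comparison rather than a threat to the trial's main conclusion.

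**What to change.** - In Table 3 and the Follow-up section, add one AE/SAE contact at the same fixed interval after every micro-TESE in both arms (for example 30 days), even when it falls after Week 16.
- Report surgical harms per operation over that equal window.
- At the interim review, show for each arm how many operated men have completed the window.
- State that the rule counting a missing AE as no event does not apply to postoperative time that was not observed.

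The cost is one extra phone or routine contact per operated man, and about 4 more weeks of safety follow-up for operated Arm A men and for SOC men operated on late. The primary endpoint, its Week 16 landmark and the sample size do not change.
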